### Study procedures

At 1, 3 months and 1 year, relevant outcome data are collected through clinical evaluation performed by the trained nurse practitioner, an orthopaedic surgeon, or resident in orthopaedic surgery. The range of motion is measured by a trained nurse practitioner who is blinded for the intervention. In the MUA group, the first follow up time is 1 month after the intervention. In the PT group, the first follow up time is 1 month after allocation. The schedule of enrolment, interventions, and assessments is shown in Fig. 4. The duration of the physiotherapy program in both groups is variable and depends on the individual result and desire of the patients. It is up to the patient to discuss this with their individual physiotherapist.

**Fig. 4 Fig4:**
[figure not shown]
Schedule of enrollment, intervention and assessments

### Sample size calculation

The SPADI is the primary outcome parameter. The sample size calculation is based on the ability to detect a difference between treatment groups of ≥13 points in the total SPADI scores. This is based on the study of Schmitt which describes a minimal clinical important difference (MCID) of 13 [36]. The study of Carette shows a standard deviation of 17 on the SPADI [37]. Based on these parameters, we calculated a sample size of 41 subjects per group with a power of 90%, alpha 0.05 and a 10% drop out rate.

### Statistical analysis

All data will be analysed in an encoded fashion. We will use CASTOR (https://www.castoredc.com/), an online data-management program, designed for medical research purposes. The patient’s demographic characteristics, EQ-5D score, range of motion at baseline, duration of symptoms before treatment starts and diabetes mellitus will be summarized and compared between groups. Also the distribution of all patient’s outcome variables will be summarized by treatment group and by time. The summaries will consist of the following descriptive statistics: number of patients involved, mean and standard deviation (or median and (inter quartile range when appropriate) for continuous variables and relative frequencies (percentages) for categorical variables. We will report the number of participants (denominator) included in each analysis and the Intention To Treat principle will be used with respect to group assignment. So, the final results of the patients will be analysed in the group to which they were allocated at the start of the study.”

The SPADI-measurements will be analysed using linear mixed modelling. The restricted maximum likelihood technique will be used for estimating the model parameters. The independent variables are time (3 levels: 1, 3 and 12 months) and treatment (2 levels), as well as their interaction. The following baseline covariates will also enter the model: SPADI at baseline, diabetes and duration of symptoms before intervention.

Primary efficacy measure is the treatment effect (MUA vs. PT) on total SPADI score after 1 month. This effect is estimated as contrast on the coefficients of the linear mixed model including the treatment-by-time interaction as mentioned above. Missing values in patients with incomplete observations will be appropriately dealt with by using the restricted maximum likelihood technique. Secondary efficacy measures are the treatment effects after 3 and 12 months and an average treatment effect over time obtained by deleting the treatment-by-time interaction. In addition, this interaction will be tested as part of the secondary efficacy analysis. Other secondary continuous outcome variables, such as OSS, NPRS, EQ-5D, WORQ-UP and ROM, will be analysed similarly to SPADI, with the baseline measurement of the outcome variable at hand as covariate. When appropriate, the outcome variable will be transformed so as to obtain normally distributed residuals.

Complications are counted by type and in total and will be analysed using Poisson regression analysis with a correction for overdispersion when appropriate. Treatment effects on complication rates will be expressed as MUA to PT rate ratios. Safety will be assessed by identifying and summarising adverse events collected throughout the study.

All estimated treatment effects will be accompanied by 95% confidence intervals and *p*-values.

Analysis will be performed by use of SPSS statistical package (IBM, version 18.0; SPSS, Chicago, Illinois).

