### Recruitment and consent

All adult patients presenting to the outpatient with the clinical diagnosis of a FS in stage two will be invited to participate in the trial. A general history is acquired. The upper extremity is examined and range of motion is measured. Conventional radiographs (true anteroposterior in the scapular plane, internal rotation with 90 degrees of flexion in the elbow and the forearm in front of the abdomen, and in maximal external rotation) are made at baseline, to rule out other pathology such as osteoarthritis. The treating orthopaedic surgeon or a member of the study staff will introduce and explain the trial to the patient and address any further questions. The patient will receive a written information leaflet together with an informed consent form. After ample time to consider participation in the trial, patients return to the outpatient clinic. After receiving verbal and written consent, eligible patients will be randomized. A secure web based randomization program (CASTOR, https://www.castoredc.com/) is used for block randomization with differing block sizes and with a randomization allocation ratio of 1. This randomization schedule is only accessible for the research coordinator. Applicants will be allocated to either the MUA group or the PT group. Only the research coordinator (who is not a treating physician) will be authorized to use the randomization software module in CASTOR to allocate patients to their intervention group, hereby ensuring concealed allocation. A participant flow diagram is shown in Fig. 1. Blinding of patients is not possible. Range of motion measurements are done by a nurse practitioner, blinded for the intervention. Crossing over (from PT to MUA) is potentially possible because patients are allowed to quit participation in the trial as a personal choice. However, the results will be analysed based on the initial treatment allocation using the intention to treat (ITT) analysis (see ‘statistical analysis’ section for more details).

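### As written, baseline SPADI has one slope for months 1, 3 and 12; a baseline-by-time term would cheaply protect the precision of the 1-month contrast

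*Protocol article*

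**What the plan says.** The Statistical analysis section of the protocol article lists the fixed effects of the linear mixed model: "The independent variables are time (3 levels: 1, 3 and 12 months) and treatment (2 levels), as well as their interaction". It then adds: "The following baseline covariates will also enter the model: SPADI at baseline, diabetes and duration of symptoms before intervention". No covariate-by-time term is named, and no covariance structure is given.

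The primary result comes from this model: "Primary efficacy measure is the treatment effect (MUA vs. PT) on total SPADI score after 1 month", and "This effect is estimated as contrast on the coefficients of the linear mixed model including the treatment-by-time interaction as mentioned above". Continuous secondary outcomes (OSS, NPRS, EQ-5D, WORQ-UP, ROM) are to be handled in the same way, each with its own baseline value as covariate.

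The Sample size calculation section uses an unadjusted SD. It cites a study that "shows a standard deviation of 17 on the SPADI" and assumes no correlation between baseline and follow-up.

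**The concern.** A main effect for baseline SPADI gives one regression slope for visits from 1 to 12 months. The slope at a visit equals the baseline-to-visit correlation times the ratio of the two SDs. The Discussion regards the condition as largely resolving by itself. If so, baseline severity may predict the score well at 1 month and poorly at 12 months. The common slope would then be pulled towards the weaker late relation and would remove too little baseline variation at the visit that decides the trial.

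Two things would be at stake. The 1-month contrast would carry avoidable residual variance. A chance baseline difference between arms of about 37 completers would also be only partly corrected at that visit.

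**Working it through.** **The plan's own figure.** Inputs from the Sample size calculation section: difference 13, SD 17, power 90%, alpha 0.05 (taken as two-sided), dropout 10%. Normal approximation: n = 2 × (1.960 + 1.282)² × (17/13)² = 35.9, so 36 per group. The exact t-test needs 37, and 37 × 1.1 = 40.7, so 41 per group. The stated 41 is reproduced. At 37 completers per arm, power without any baseline adjustment is Φ(13 / (17 × √(2/37)) − 1.96) = Φ(3.289 − 1.96) = 90.8%.

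**Formulas.** Let b₁, b₃, b₁₂ be the true baseline slopes (correlation × SD at visit / SD at baseline), and c the common slope.
- 1-month residual variance with visit-specific slopes: V₀ = SD₁² × (1 − ρ₁²).
- With a common slope: V₁ = V₀ + (b₁ − c)² × Var(baseline).
- Under an unstructured residual covariance W, c is the GLS-weighted mean of the slopes, with weights proportional to W⁻¹1. Under compound symmetry, c is their simple mean.

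**Assumptions.** The article gives no baseline-to-follow-up correlations, no visit-specific SDs and no covariance structure. All correlations below are assumed. Baseline SD is 17, and residual correlations are 0.5 (months 1–3), 0.5 (3–12) and 0.3 (1–12).

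**One case in full** (correlations 0.6/0.4/0.2, SD 17 throughout). Slopes are 0.6, 0.4, 0.2. Residual SDs are 13.60, 15.58, 16.66. GLS weights are 0.537, 0.184, 0.279, so c = 0.322 + 0.074 + 0.056 = 0.452. V₀ = 289 × 0.64 = 184.96. V₁ = 184.96 + (0.148)² × 289 = 191.3. The ratio is 1.034, so the variance is 3.4% too large and the SE 1.7% too large. In patients, 82 × (1 − 1/1.034) = 2.7. Under compound symmetry c = 0.4, V₁ = 184.96 + 0.04 × 289 = 196.5, and the ratio is 1.062.

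**Range of cases** (excess 1-month variance):

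| Correlations 1/3/12 | SDs 1/3/12 | Unstructured | Compound symmetry |
|---|---|---|---|
| 0.5/0.5/0.5 | 17/17/17 | 0% | 0% |
| 0.5/0.4/0.3 | 17/17/17 | 1.0% | 1.3% |
| 0.6/0.5/0.4 | 17/17/17 | 1.1% | 1.6% |
| 0.6/0.4/0.2 | 17/17/17 | 3.4% | 6.2% |
| 0.7/0.4/0.1 (steep fall) | 17/17/17 | 5.9% | 17.6% |
| 0.6/0.3/0.0 (steep fall) | 17/17/17 | 7.1% | 14.1% |
| 0.6/0.4/0.2 | 17/17/12 | 11.8% | 7.5% |
| 0.6/0.4/0.1 | 20/18/12 | 21.9% | 10.6% |

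The unstructured figures move by a few points with the assumed correlations between visits. For 0.7/0.4/0.1 other choices gave SE losses of 0.8–2.5%.

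**Chance imbalance.** A 5-point baseline difference leaves 5 × (b₁ − c) uncorrected: 5 × 0.148 = 0.7 points in the worked case, about 0.4 with the flatter declining patterns, and 2.2 only in the last row.

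**Power at 37 completers per arm** (month-1 SD 17). For 0.6/0.4/0.2 it is 98.4% with visit-specific slopes (residual SD 13.6), 98.1% with a common slope under an unstructured covariance (13.83) and 97.9% under compound symmetry (14.02). The lowest value in any row with month-1 SD 17 is 96.5% (0.5/0.4/0.3, compound symmetry). More generally, for any c between 0 and b₁ the residual variance stays below the unadjusted variance, so power cannot fall below the unadjusted 90.8%.

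**Bias.** In simulations of 1,500 trials per pattern (complete data, unstructured covariance, true effect −13) the adjusted estimates averaged −12.97 to −13.12 with a common slope and −12.95 to −13.12 with visit-specific slopes. Empirical SEs were 3.22 against 3.16 for 0.6/0.4/0.2, and 2.77 against 2.73 for 0.7/0.4/0.1.

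**The case against.** The strongest reply is that nothing here is wrong. Adjusting for baseline as a prespecified main effect is a valid analysis, and most of its gain is kept: in the worked case the residual SD falls from 17 to 13.8, against 13.6 at best. A condensed article may also leave a covariate-by-time term to a fuller plan, and the text does not exclude one. Both arguments stand, and they limit this point to a refinement. They do not remove it, because the section lists the model terms one by one and names a single interaction.

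The premise is also open. The Background section reports residual pain in up to 50% of patients, restricted motion in up to 60% and a mean duration of 30.1 months. Patients whose symptoms began a year or more ago are excluded, so the 12-month visit falls about two years after onset or earlier, apart from the wait for MUA. Baseline severity could still matter then. MUA may also act within days, which could weaken the baseline relation at month 1 in that arm.

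A reader might infer that the primary contrast is under-adjusted as a matter of fact, or that a loss of 12–22% should be expected. The document supports neither. The first needs slopes that differ by visit. The second needs month-12 SDs that appear nowhere in it, the only stated SD being 17.

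**Conclusion.** The point holds as a conditional, low-severity matter of precision. Followed as written, the model gives baseline SPADI one slope. If that slope declines over follow-up, the 1-month contrast loses some precision. With SD 17 throughout and correlations falling no faster than 0.6/0.4/0.2, the loss is roughly 1–4% of the 1-month variance under an unstructured covariance (about 1 to 3 of the 82 patients) and up to about 6% under compound symmetry. With equal slopes it is zero. Larger losses need a steeper assumed fall in correlation or a shrinking SD at month 12.

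Two stronger readings fail. The estimate is not biased by the common slope under randomisation with complete data, so this is no question of validity. The trial is not underpowered because of it, since 41 per group was derived from the unadjusted SD. In the 20/18/12 row computed power does drop below 90% (93.8% to 88.6% under an unstructured covariance). That case assumes a month-1 SD of 20, with which unadjusted power would already be only 79.8%.

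**What to change.** In the Statistical analysis section, add a baseline SPADI-by-time interaction so that the baseline slope is specific to each visit. Do the same for the baseline value of each continuous secondary outcome analysed in the same way. Keep the 1-month treatment contrast as primary. If a common slope is intended, say so and give the reason.

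The cost is one term with two degrees of freedom per model. No new data are needed, and neither the primary contrast nor the sample size changes. If the slopes turn out equal, almost nothing is lost. Settling the term before outcome data are seen also avoids a later choice between two models.

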### Study population

This study focusses on patients with a clinical diagnosis of a stage two FS. This is defined as symptoms of pain and stiffness, predominantly in one shoulder, persisting ≥3 months, without preliminary trauma which led to an anatomic abnormality. Characteristically, the pain is most severe at the end of the range of motion. Pain must be diminished compared to the maximum amount of pain in stage one of the condition.

In order to be eligible to participate in this trial, patients must meet all of the following criteria:Age > 18 years and ≤70 yearsRestriction of passive motion in the glenohumeral joint of ≥30° in external rotation and at least a second plane of movement with ≥30°restriction (compared to the contra-lateral side)Unsuccessful conservative therapy within the previous 3 months. This is considered as insufficient improvement after an intra-articular corticosteroid infiltration and physiotherapy treatment during at least 6 weeks.

Patients with diabetes are eligible for participation in this trial.

If any of the following criteria will apply, patients will be excluded from participation:Numeric Pain Rating Scale at rest ≥7Onset of symptoms ≥1 year agoOsteoarthritis of the glenohumeral joint, Kellgren-Lawrence osteoarthritis grading scale ≥2Previous surgery to the shoulderSystemic inflammatory joint diseaseEvidence of a complete rotator cuff tear on physical examination, ultrasound images or MRINeurological disorders of the upper limbTherapeutic anticoagulation which can not be interrupted without bridging therapyOther known shoulder pathology such as infection or tumorContra-indication to corticosteroid injection, allergy to contrast or local anaestheticInability to give informed consent and fill out questionnaires

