Secondary outcome measures consist of;Oxford Shoulder Score (OSS), which reflects both function and pain of the shoulder. The OSS is a patient reported questionnaire, which consist of 12 questions related to pain and function of the arm in daily life. Items are scored on a zero to four point scale. This leads to an OSS score between 0 (worst) and 48 (best) [30].Shoulder pain at rest, and during activity; Pain level will be determined using the The Numeric Pain Rating Scale (NPRS). The NPRS is a validated 11-point score to assess pain, which represents a valid measure of pain with a good construct validity. The NPRS ranges from zero to ten, in which zero expresses no pain and ten expresses the worst pain possible.Health related quality of life, determined using the three level EuroQol five-dimensional questionnaire (EQ-5D 3-L). The EQ-5D is a five question standardised questionnaire scoring on five domains: mobility, self-care, usual activities, pain/discomfort, and anxiety/depression. It also includes a VAS self rating health scale on which patients rate their health state (0 is worst imaginable health and 100 is best imaginable health) [31]Passive Range of Motion (ROM) is measured by a goniometer. Forward flexion and abduction in the standing position, external rotation measured with the arm held at the side and the elbow in 90° flexion. Internal rotation is estimated to which height the patient can reach on his back, appointed to the highest vertebral level of the wrist.The ability to work is evaluated by two questionnaires. The WORQ-UP is a patient reported questionnaire with 17 items of common physical tasks at work, scored on a five point scale [32]. Single item work ability Index is a single question whereby patients rate their ability to perform physical tasks at work on a ten point scale. Zero indicates no ability to perform work with any physical task at all. Ten indicates the best period in life to perform physical tasks at work [33–35]. Absenteeism at work is evaluated with a single question where patients register the amount of days absent at work past month due to complaints of the shoulder.Duration of symptoms is determined. Patients are asked to estimate the duration of symptoms in weeks from MUA or allocation to the PT group until almost full recovery.Two anchor questions will be asked regarding the change that is experienced since the start of treatment considering pain and daily functioning. This is reported on a seven-point scale. These questions are based on an advice to use them from the division shoulder and elbow from the Dutch Orthopaedic Society.Quantity of physiotherapy treatment sessionsUsage of analgesics (acetaminophen, NSAID’s or opioids)Number of repeated corticosteroid infiltrationsNumber of complications (infection, fracture, dislocation, neurovascular compromise, subsequent or intervention) will be registered and evaluated.

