
Passive range of motion is the only blinded outcome measure. All other outcomes are assessed unblinded or self reported.

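### The external-rotation analysis omits the contralateral range that eligibility already requires, probably giving up some precision on the only blinded outcome; a low-priority improvement

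*Protocol article*

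**What the plan says.** Under Statistical analysis, the secondary continuous outcomes, ROM among them, are to be handled in the same way as SPADI, "with the baseline measurement of the outcome variable at hand as covariate". The SPADI model that this refers to is specified just before: "The following baseline covariates will also enter the model: SPADI at baseline, diabetes and duration of symptoms before intervention". On the natural reading, each ROM model therefore holds the affected shoulder's own baseline, diabetes and symptom duration, together with treatment, time and their interaction. The other shoulder's range is not mentioned in that section.

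Under Study population, the required restriction of passive motion is at least 30° in external rotation, plus "at least a second plane of movement with ≥30°restriction (compared to the contra-lateral side").

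Under Outcome measures, ROM is described as "Forward flexion and abduction in the standing position, external rotation measured with the arm held at the side", with internal rotation estimated as a vertebral level. The same section states: "Passive range of motion is the only blinded outcome measure".

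**The concern.** Eligibility defines stiffness as a deficit from the patient's other shoulder, but the analysis drops that reference. The affected side's baseline cannot separate a naturally less mobile patient with a small deficit from a very mobile patient with a large one, although the range each can regain differs. As shoulders recover, follow-up range should move away from the stiff baseline and towards the patient's own normal. Differences in normal mobility then remain in the residual variance.

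What is at stake is the width of the ROM intervals. The primary SPADI is self-reported by unblinded patients, gain in range of motion is part of the stated hypothesis (Background), and the sample size was set on SPADI alone. No power is assured for ROM, so precision on the one blinded outcome is worth having if it is cheap.

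**Working it through.** **The plan's own figure.** Inputs from Sample size calculation: difference 13, SD 17, power 90%, alpha 0.05 (two-sided assumed), dropout 10%.

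- Normal approximation: n = 2 × (1.960 + 1.282)² × 17² / 13² = 35.9, so 36 per arm; 36 / 0.9 = 40.
- Exact t-test: 37 per arm; 37 / 0.9 = 41.1, so 42; or 37 × 1.10 = 40.7, so 41.

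The stated 41 per group reproduces within one patient. It concerns SPADI only; the document gives no SD, target difference or power for ROM. The number evaluable is 41 × 0.9 = 36.9, so 37 per arm.

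**Effect of one more baseline covariate.** Let r be the partial correlation of contralateral range with follow-up range, given treatment and the planned covariates. The variance of the treatment contrast at one visit is multiplied by about

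(1 − r²) × (df₀ − 1) / (df₁ − 1),

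where df₀ = 2 × 37 − 2 − 3 = 69 without the covariate and df₁ = 68 with it. The second term is 68 / 67 = 1.015. The interval width changes by the square root of the product. The document gives no r, so a range is shown:

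| r (assumed) | Variance factor | Change in CI width | Equivalent n per arm (from 37) |
|---|---|---|---|
| 0 | 1.015 | +0.7% | 36.5 |
| 0.1 | 1.005 | +0.2% | 36.8 |
| 0.2 | 0.974 | −1.3% | 38.0 |
| 0.3 | 0.924 | −3.9% | 40.1 |
| 0.4 | 0.853 | −7.7% | 43.4 |
| 0.5 | 0.761 | −12.8% | 48.6 |

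Break-even is where 1 − r² = 67 / 68, that is r = √(1/68) = 0.12. Below that the covariate costs slightly more than it returns.

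**Why later visits should gain more.** A simulated single-visit ANCOVA illustrates the direction. The assumptions, none of them from the document, are 37 per arm, contralateral external rotation SD 15°, a deficit of at least 30°, 6° measurement error, and a fraction of the deficit regained that varies between patients.

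- SD of that fraction 0.2: adding the contralateral value took the standard error from 2.92 to 2.84 when 20% of the deficit was regained (variance −5%), and from 3.23 to 2.82 when 80% was regained (−24%).
- SD of that fraction 0.3: the variance reductions were 2.5% and 15%.

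This model builds in recovery towards the other shoulder. It shows how the gain grows with recovery, not that a gain exists.

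**The case against.** The strongest reply is that nothing here is an error. The stated model is standard and valid, no other section contradicts it, and an extra prognostic covariate for a secondary outcome is a refinement. That stands, and it sets the low priority. It does not remove the point, because the article names the covariates itself and leaves out a reference that its own eligibility rule needs.

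Four stronger readings are tempting, and the document does not support them.

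- **That the ROM models adjust for the affected shoulder's baseline alone.** They do not: analysing ROM like SPADI brings in diabetes and symptom duration.
- **That precision is certainly lost.** The loss depends on r, which is not given, and at r of about 0.1 or less there is none.
- **That contralateral values are at hand for every ROM outcome.** Eligibility fixes external rotation and one further plane, which is unspecified and may differ between patients. The article also does not say that the contralateral degrees are stored as study data. Adding the covariate to flexion or abduction regardless could lose patients from those models or force imputation.
- **That the other shoulder is always a healthy reference.** The condition is defined by "symptoms of pain and stiffness, predominantly in one shoulder, persisting ≥3 months", so the other side may be mildly affected. The covariate is then less informative, though still measured before randomisation.

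Adjustment also does not turn the result into a measure of residual deficit. The contrast remains a mean difference in degrees.

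**Conclusion.** The point holds as a cheap, optional gain in precision. The contralateral range must be assessed in external rotation for every patient before randomisation, it is a legitimate covariate, and the stated model leaves it out. The size rests on an assumed r. With 37 evaluable per arm, interval width changes from +0.7% (r = 0) through −3.9% (0.3) and −7.7% (0.4) to −12.8% (0.5), and the gain is expected to be larger at later visits. The worst case is small and the plausible case is modest.

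A reader might infer that the omission biases the ROM results or weakens the trial's main conclusion. It does neither: the randomised ROM comparison is valid as planned, and narrower ROM intervals would not change the unblinded nature of SPADI. Low priority.

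**What to change.** Record contralateral passive external rotation in degrees at the eligibility assessment. In Statistical analysis, add one sentence prespecifying it as a further covariate in the external-rotation mixed model, alongside own baseline, diabetes and symptom duration. An interaction of this covariate with time may be added if wished, since its value is expected to grow over the visits.

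Extend this to flexion and abduction only if the contralateral value for that plane is recorded in all patients. Leave internal rotation (a vertebral level) and the provision to transform outcomes as they are.

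The sentence should be fixed before outcome data are seen, since a covariate chosen afterwards is open to challenge. The cost is one recorded value per patient and one degree of freedom in the model (more with the time interaction). The planned 41 per group does not change.

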Traditionally, manipulation under anaesthesia (MUA) is a well-established treatment for FS if conservative treatment fails [13, 18, 19]. MUA is a short and relative simple procedure by which capsular adhesions are torn apart by manipulation, with the potential to rapidly restore the range of motion and reduce symptoms within days after the procedure [20]. However, the role of MUA in the treatment of FS is still controversial because it might lead to serious complications in rare cases such as a humeral fracture, glenohumeral dislocation, and brachial plexus traction injury [21, 22]. Other potential complications are intra-articular damage to the cartilage, glenoid rim fractures, or rotator cuff tears [23]. On the other hand, rotator cuff integrity was maintained after MUA in the study of Atoun [24] and the reported complication rate in cohort studies and reviews of 0.5% is rather low [16, 20, 25].

There is only one randomized controlled trial, in which MUA is compared to conservative treatment. Kivimäki et al. conducted a randomized trial with 110 patients in which MUA in combination with a home exercise program was compared to a home exercise program alone [14]. A small difference regarding mobility and pain in favour of the manipulation group was found, but was considered clinically unimportant. However, 34% of patients were lost to follow up after 6 months, and only 3 patients of the manipulation group were available for follow up at 12 months. Therefore, no firm conclusions can be drawn based on that study. Moreover, the rehabilitation after MUA was far different from the physiotherapy protocol in the current study. In the study of Kivimäki et al., physiotherapy advice was given in two sessions and written instructions for a home exercise program were provided. We suppose that an initial period of one to 2 weeks of intensive physiotherapy treatment after MUA is essential to prevent recurrence of restrictions. Therefore, we advocate a more aggressive rehabilitation with intensive stretching and range of motion exercises in the first weeks after MUA to preserve the obtained range of motion.

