In the current situation in our hospital, a variability in the threshold to decide for MUA between the different individual orthopaedic surgeons in the treatment of FS was noticed. This variability was also demonstrated in a survey among Dutch and Belgian orthopaedic surgeons [26]. In addition, we found that MUA was carried out most frequently at our hospital. In anticipation of the current protocol for an RCT, we reviewed our own results after manipulation in a retrospective cohort study. In 2 years, 89 patients were treated by manipulation for a FS. Eighty-five percent of the patients were satisfied with the procedure with good results. No complications were noticed. ([name] et al. *Acta orthopaedica Belgica* 2017, in press).

The objective of this trial is to evaluate the effectiveness of MUA followed by a PT program compared to a PT program alone in the treatment of patients with a stage two FS. We hypothesize that the course of the disease can be shortened with MUA with a quicker functional recovery and gain in range of motion and a subsequent faster return to work compared to physiotherapy treatment.

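### The planned Poisson MUA-to-PT rate ratio for complications will very probably not be estimable at the protocol's own complication rate, and one listed complication is too unclear to count

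*Protocol article*

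**What the plan says.** The Statistical analysis section of the protocol article fixes the method: "Complications are counted by type and in total and will be analysed using Poisson regression analysis with a correction for overdispersion when appropriate". It continues: "Treatment effects on complication rates will be expressed as MUA to PT rate ratios". The same section attaches a 95% confidence interval and a p-value to every estimated treatment effect, and separately plans a descriptive summary of adverse events. It gives no rule for empty or sparse cells.

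The Background gives the only complication figures for MUA. It notes that "the reported complication rate in cohort studies and reviews of 0.5% is rather low". It also describes the hospital's own retrospective series ("In 2 years, 89 patients were treated by manipulation for a FS"), in which no complication was seen.

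The Outcome measures section lists the complications as infection, fracture, dislocation and neurovascular compromise, then a last item in which the words subsequent and intervention are joined by or. That item does not parse; a subsequent intervention is the most plausible meaning. Recruitment and consent allows crossover from PT to MUA, ties it to patients choosing to leave the trial, and analyses patients by initial allocation. No crossover rate is given.

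**The concern.** A rate ratio needs events in both arms to be finite and non-zero. The protocol's own figures suggest that even the MUA arm will probably have none, and splitting the counts by type thins them further. The overdispersion correction deals with excess variance and does nothing for empty cells.

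The Discussion says that the safety of MUA will be critically assessed, and the Background calls MUA controversial because of rare serious complications. If the headline safety statistic is degenerate, the reader does not learn what the trial can show, which is an upper bound on the complication rate.

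The unclear list item adds a second problem. If further interventions count, and if MUA received by a PT patient is recorded as one, the complication total combines failure of treatment with harm from treatment.

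**Working it through.** **Inputs.** The Sample size calculation states "we calculated a sample size of 41 subjects per group with a power of 90%, alpha 0.05 and a 10% drop out rate", to "detect a difference between treatment groups of ≥13 points in the total SPADI scores", from a study that "shows a standard deviation of 17 on the SPADI". Allocation is by "block randomization with differing block sizes and with a randomization allocation ratio of 1". The MUA complication rate is 0.5%, and the own series has 0 of 89 (both Background). The PT complication rate is not given, so it is varied below. Equal follow-up and at most one event per patient are assumed.

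**The plan's own figure.** Normal approximation, two-sided alpha (sidedness assumed): n = 2 × (1.960 + 1.282)² × 17²/13² = 35.9, so 36 per arm; 36/0.9 = 40. The t-test version needs 37 per arm; 37 × 1.1 = 40.7, so 41, or 37/0.9 = 41.1, so 42. The stated 41 is reproduced to within one patient and is used below.

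**Expected MUA-arm procedural complications.** Expected count = n × p and P(none) = (1 − p)^n, with n = 41.

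| MUA rate | Expected | P(none) |
|---|---|---|
| 0.5% (cited) | 0.205 | 0.81 |
| 1% | 0.41 | 0.66 |
| 2% | 0.82 | 0.44 |
| 4.1% (upper two-sided 95% limit for 0/89: 1 − 0.025^(1/89)) | 1.7 | 0.18 |

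With 37 completers at 0.5%, the expected count is 0.185 and P(none) is 0.83. Spread over the four clearly named types, the average is 0.205/4 = 0.05 events per type.

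**Chance of a finite, non-zero ratio.** P(events in both arms) = [1 − (1 − p)^41] × [1 − (1 − q)^41], where p is the MUA rate and q the assumed PT rate.

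- p = q = 0.5%: 0.186 × 0.186 = 0.035. P(no event in either arm) = 0.66, which leaves about 0.30 for events in one arm only.
- p = q = 2%: 0.563 × 0.563 = 0.32. P(no event in either arm) = 0.19.
- p = 4.1%, q = 0.5%: 0.15.
- p = 4.1%, q = 2%: 0.46.
- q = 0: never.

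**What the model returns with one empty arm.** A Poisson regression fitted to 1 event in MUA and 0 in PT (41 each) gives a log rate ratio of about 20, a standard error of about 16,000 and p = 0.999. With 0 and 4 events it gives about −21, with a standard error of about 13,000. The exact conditional interval for 1 versus 0 runs from 0.026 to infinity.

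**What the trial can say with no events.** For 0/41 the exact two-sided 95% upper limit is 1 − 0.025^(1/41) = 0.086.

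**The case against.** Several counter-arguments deserve weight.

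- The 0.2 covers only procedural complications in the MUA arm. It is not the expected count for the whole list or for both arms, and the hospital's 0/89 is compatible with about 1.7 MUA events. This stands. Even so, with 4.1% in MUA and 2% in PT, the chance of events in both arms stays below one half.
- The protocol does not specify Wald intervals. Exact intervals for a rate ratio give a finite bound on one side when only one arm has events, and a dispersion factor can be computed once any event occurs. This stands too: the fault lies with the ratio as the reported quantity and with standard model-based output, not with every conceivable interval.
- Descriptive adverse-event reporting is planned in any case, and a sparse-data fallback could sit in an analysis plan that is not shown. Descriptive reporting does soften the consequence. But the ratio, its interval and its p-value are fixed in this text, by type as well as in total.
- Exact tests also have almost no power at these counts. True; their advantage is that they remain defined.

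A reader might go further and infer that crossovers will make MUA look far safer than physiotherapy. With assumed crossover of 5%, 10% or 20%, PT would gain 41 × 0.05 = 2.1, 4.1 or 8.2 events against 0.2 in MUA, a ratio of about 0.10, 0.05 or 0.025. With 0 versus 8 events the exact interval would be 0 to 0.59. The document does not support this as a prediction. It states no crossover rate and never says that MUA in a PT patient is a complication. It links crossover to leaving the trial, so the event may go unrecorded. The comparison also sets procedural events in one arm against interventions in the other, although repeat interventions after MUA could count as well.

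**Conclusion.** The concern holds for the rate ratio. At the cited 0.5%, P(no MUA-arm procedural complication) is 81%. With the same rate assumed in PT, the ratio is finite and non-zero with probability of about 3.5%; at 2% in both arms this rises only to about 32%. The planned ratio will therefore very probably be zero, infinite or undefined, most of all by type. These figures rest on 41 patients per arm, equal follow-up and an assumed PT rate.

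The list item is a definitional ambiguity to be resolved. Mixing of failure and harm is a plausible risk if the item means subsequent intervention and if crossovers are recorded and counted. Its size, and even its net direction, cannot be derived from the document.

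This is a secondary safety analysis. The SPADI comparison and the sample size are untouched.

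**What to change.** 1. Replace the Poisson rate ratio with the number of patients with at least one complication per arm, exact (Clopper-Pearson) 95% intervals, and an exact between-arm comparison (risk difference or Fisher test). Keep the counts by type as description.
2. Correct the last item of the complication list so that its meaning is clear.
3. Report subsequent interventions in both arms, including PT-to-MUA crossover, as a separate outcome outside the procedural complication total, and say how those occurring after a patient leaves the trial are recorded.
4. State in advance that 0/41 would exclude only complication rates above about 8.6% (two-sided 95%).

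The cost is wording only. The downside is that the exact comparison has little power, and that the safety conclusion becomes a bound on a rate and not a ratio between arms.
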